### Study design and treatment schedule

The REMOTUX trial is designed and conducted at the National Center for Tumor disease (NCT) at the University Medical Center Heidelberg. It is an investigator-initiated, prospective, open-label, single-arm, and single-center early exploratory predictive study.

The first ^18 ^F-FDG PET-CT (and liver ultrasound, if available), is conducted at baseline followed by the run-in treatment phase with cetuximab therapy at days 1 and 8 (400 mg/m^2 ^bsa and 250 mg mg/m^2 ^bsa respectively). At day 14, the second ^18 ^F-FDG PET-CT (and liver ultrasound, if available) is performed. Subsequently, patients are treated according to the Folfiri-cetuximab regimen as an active and approved first-line regimen for metastatic colorectal carcinoma. According to the clinical standards at the NCT Heidelberg, the Folfiri-cetuximab regimen is recommended to follow the schedule of Table 1. At day 56, the early clinical response is evaluated with a routine CT-scan in comparison to the baseline analysis. Depending on the clinical response, treatment will be continued according to the choice of the responsible physician. It is recommended that, in case of response, treatment will be continued with cetuximab and the Folfiri regimen until disease progression or patients are unable to tolerate the therapy. Patients are followed-up every 3 months. Patients are followed until death from any cause or until 24 months after the last patient has ended trial treatment. A flowchart is given in Table 2.

**Table 1 T1:** Folfiri-Cetuximab-regimen, to be repeated every 2 weeks

Chemotherapeutic agent	**Dosage (mg/m**^**2**^**)**	Treatment day
Cetuximab	250 *	1, 8
	* 400 at first application	
Irinotecan	180	1
Folinic Acid	400	1
5Fluorouracil (bolus)	400	1
5Fluorouracil (46 hours)	2400	1

**Table 2 T2:** Flowchart (diagnostic procedures and run-in treatment)

Baseline	Day 1	Day 8	Day 14		Day 56
PET-CT	Cetuximab	Cetuximab	PET-CT	Folfiri-Cetuximab	CT

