#### Sample size calculation

The trial will include 35 patients who are evaluable for the primary analysis. The sample size/power calculations were based on the Wilcoxon rank sum test (two-sided testing; α = 5%) in the form proposed by Noether [13] and implemented in the software package nquery advisor 6.01 [Statistical Solutions, Inc.: nquery advisor^® ^6.01. Saugus, MA (2005)]. This form of the power calculation assumes that the alternative hypothesis is expressed as a probability P(Y > X), which, in our context, is the probability that a random responder has a higher value of ΔSUV than a random nonresponder. Note that the probability P(Y > X) is identical to the AUC of the population ROC of ΔSUV with respect to the binary response. It should be observed that the group sizes of this test cannot be determined in advance. Rather, the number of responders follows a binomial distribution with n = number of evaluable patients, and binomial probability r = probability of response. Therefore, the power of the test is a weighted sum of the values of the power calculated for each possible constellation of group sizes of responders and nonresponders, the weights being the binomial probabilities that a particular constellation arises. Assuming that the values of ΔSUV in the groups of clinical responders and nonresponders, resp., are represented by independent normally distributed variables with equal variances, and assuming that the true early clinical response rate of r is in the range 40% to 60%, the projected sample size of 35 evaluable patients is sufficient to detect an AUC of ΔSUV (calculated with respect to response) of 0.8 with power 84.1% (the maximum power of 85.7% being attained for r = 50%). It should be noted, however, that the true clinical response rate r is unknown. For r = 65% (instead of r = 60%) the estimated power for an AUC = 0.8 drops to 81.9%. Therefore, the slight overpowering if r is in the assumed range of values (40% to 60%) appears justified. Assuming that about 10% of the enrolled patients are not evaluable for the primary analysis, it is expected that the total number of patients to be enrolled in the study is 39. It is noteworthy that, under the assumptions specified above, 35 evaluable patients are also sufficient for detecting with power > 80% an AUC of 0.8 in the exploratory analysis of the main end point by means of a univariate logistic regression analysis (calculations based on 10000 computer simulations runs).

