#### Statistical analysis

The null hypothesis that ΔSUV has no predictive power for early response will be tested using the Wilcoxon rank sum test (2-sided test, α = 5%). The null hypothesis of this test is that the distributions of ΔSUV in the groups of early clinical responders and nonresponders are identical. The AUC of ΔSUV with respect to the response status will be calculated along with bias-corrected and accelerated bootstrap 95% confidence intervals, as described by Zhou [14]. If, based on the results, a cut-off for predicting response is selected post hoc, then using the bootstrap (and with the same criterion as used in the selection) bias-corrected indices of accuracy will be estimated from the data. Logistic regression models will be used to further explore the relationship between ΔSUV and early clinical response, and, in particular, whether any confounder for the relationship between ΔSUV and early clinical response can be determined. The model assumption of a linear relationship between ΔSUV and the logit of endpoint will be explored by visual inspection. Standard methods for right-censored data will be used for analyzing PFS and OS. The Cox Regression model will be used to examine the influence of ΔSUV and of early clinical response on PFS and OS. For the evaluation of the predictive value of ΔSUV for clinical tumor response all patients will be analyzed for whom the variable ΔSUV as well as the response measurement is available. The assessment of safety will be based mainly on the frequency of adverse events and on the number of laboratory values that fall outside of pre-determined ranges and/or show prominent worsening from baseline during the study phase. Missing values will not be replaced or imputed

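### The laboratory safety measure counts abnormal values and states no patient count or denominator, so on its own it does not show what share of patients had an abnormality

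*Protocol article*

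**What the plan says.** The Statistical analysis section gives the safety assessment one sentence with two main measures. The first is adverse events: "The assessment of safety will be based mainly on the frequency of adverse events". The second is laboratory data: "the number of laboratory values that fall outside of pre-determined ranges and/or show prominent worsening from baseline during the study phase". Both laboratory criteria, being out of range and having worsened, are counted in values. The sentence gives no number of patients, no denominator and no adjustment for samples taken, and it does not say when the study phase ends. The same section adds: "Missing values will not be replaced or imputed".

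Three other places bear on how many values a patient contributes:

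- *Safety aspects and adverse events (AEs)*: each adverse event is followed until it resolves, the altered laboratory parameters return to normal, or the condition becomes stable.
- *Study design and treatment schedule*: after the day 56 assessment, "treatment will be continued according to the choice of the responsible physician". For responders it is only a recommendation that "treatment will be continued with cetuximab and the Folfiri regimen until disease progression or patients are unable to tolerate the therapy".
- *Sample size calculation*: "it is expected that the total number of patients to be enrolled in the study is 39".

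**The concern.** A reader of a safety report wants to know what share of patients had a laboratory abnormality. A count of abnormal values does not answer that. One patient whose parameter stays abnormal is counted at every draw, while a patient with one abnormal value is counted once. The total therefore mixes how many patients were affected, how long each abnormality lasted, and how often blood was taken.

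The adverse event follow-up rule makes this more than a theoretical worry. Where an abnormal laboratory value belongs to an adverse event, following it to normalisation or stability can produce repeat tests, and each one that is still abnormal adds to the total. Conversely, because missing values are not replaced, a patient who leaves early simply contributes fewer values. At stake is how well one of the two main safety measures can be read; no efficacy conclusion is involved.

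**Working it through.** **Inputs from the article.** The laboratory sentence contains no figure to reproduce. The only figure needed is the expected enrolment. From "The trial will include 35 patients who are evaluable for the primary analysis" and "about 10% of the enrolled patients are not evaluable for the primary analysis": 35 / (1 − 0.10) = 38.9, rounded up to 39. This agrees with the article.

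**Inputs that are assumptions.** The article prints no laboratory schedule. I assume the same number of draws, s, for all 39 patients, look at one parameter, and vary s.

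**Check 1: how many patients can stand behind one count.** Take 32 abnormal values. A patient can contribute at most s of them, so at least 32/s patients (rounded up) are affected. If each affected patient contributes one, 32 patients are affected.

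| Draws per patient (s) | Values in total (39 × s) | Fewest patients | Most patients |
|---|---|---|---|
| 2 | 78 | 32/2 = 16 (16/39 = 41%) | 32 (32/39 = 82%) |
| 4 | 156 | 32/4 = 8 (8/39 = 21%) | 32 (82%) |
| 8 | 312 | 32/8 = 4 (4/39 = 10%) | 32 (82%) |
| 12 | 468 | 32/12 = 2.7, so 3 (3/39 = 8%) | 32 (82%) |

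At s = 8 the summary reads 32 whether 10% or 82% of patients were affected. Dividing by the values taken does not separate the two cases: 32/312 = 10.3% in both.

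**Check 2: how the count moves when the risk does not.** Suppose 20% of the 39 patients are affected (0.20 × 39 = 7.8 expected) and are abnormal at every draw. The expected count is 7.8 × s:

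- s = 2: 15.6
- s = 4: 31.2
- s = 8: 62.4
- s = 12: 93.6

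The count rises sixfold (93.6 / 15.6 = 6) while the share of patients affected stays at 20%.

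**What does not depend on the assumptions.** With a single draw per patient, values and patients coincide. With more than one, they need not. The draws assumed set the width of the range, not whether the ambiguity exists.

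**The case against.** The strongest reply is that this is a condensed article. The layout of laboratory tables, the denominator and the grading are usually settled in the analysis plan, which is not shown, and the article does not print its pre-determined ranges either. That stands for the layout. It does not dispose of the counted unit, which the sentence states; an analysis plan that follows the sentence would inherit it.

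Other parts of the reply stand and limit the point:

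- A reader might infer that the plan rejects counting patients. It does not. The sentence states no patient-level table, but it excludes none.
- A reader might infer that the count has no valid denominator because values within a patient are correlated. That goes too far. No denominator is stated, but no test or interval on these counts is described, and correlation does not invalidate a descriptive count.
- A reader might infer that the count is weighted towards responders because they are treated for longer. The article supports this only conditionally: continued treatment is a recommendation for responders after day 56, and the study phase may end at day 56.
- The extremes in the illustration show what is possible, not what is likely.
- Laboratory abnormalities may also appear among the adverse events, so the laboratory count is not the only route by which they would be seen.
- Safety is not among the objectives listed under Study objectives, and no decision rule uses the count.

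**Conclusion.** The point holds as a minor one. The article names the laboratory value as the unit for one of its two main safety measures and states no patient count or denominator. Used alone, that count depends on sampling and repeat testing and cannot be turned into a share of patients: under the assumed 8 draws in 39 patients, 32 abnormal values fit anything from 4 patients (10%) to 32 patients (82%).

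The size of that range rests on the assumed number of draws, equal for all patients, and on all 39 being sampled. The direction rests only on patients having more than one sample. The primary Wilcoxon comparison, the power figures and the enrolment of 39 are unaffected.

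**What to change.** Change the laboratory part of the safety sentence so that the main summary is, for each parameter, the number and percentage of patients with at least one post-baseline value that is out of range or prominently worsened from baseline. The denominator is patients with at least one post-baseline value of that parameter. State when the study phase begins and ends. Keep counts of values, if wanted, as a secondary description next to the number of values taken.

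Exact confidence intervals, worst grade per parameter, and separate tables for the run-in and the Folfiri-cetuximab period would be useful but are optional.

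The cost is one sentence and a different table from data already collected. The article reports 7 patients included at the time of writing, so the change could be made well before analysis.

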### Safety aspects and adverse events (AEs)

Due to the use of a safe and well known therapeutic regimen, there are only few AEs to be expected. Skin toxicity ≤ grade 3 caused by cetuximab will not be reported as an AE. In this trial, all AEs that occur after the patient has signed the informed consent document will be documented. All patients who have AEs, whether considered associated with the use of the trial medication or not, are monitored to determine the outcome. The clinical course of the AE will be followed-up until resolution or normalization of changed laboratory parameters or until it has changed to a stable condition.

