## Background

Colorectal cancer is one of the three most common types of cancer in men and in women. It is estimated that about 1.2 million new cases were diagnosed worldwide in 2008 and approximately 609.000 deaths occurred [1]. The 5-year overall survival rate for patients with metastatic disease in the western world has increased during the last decade and is nowadays reported to reach about 10% [1]. The median overall survival for patients treated with active combination chemotherapies and monoclonal antibodies (mABs) is nowadays in excess of two years [2].

The epidermal growth factor receptor (EGFR) mAB cetuximab has proven activity in metastatic colorectal cancer. In combination with an irinotecan-containing cytotoxic regimen (Folfiri), cetuximab significantly increases progression free survivial (PFS) in first-line therapy compared to the Folfiri regimen alone [3]. In patients with metastatic colorectal cancer that no longer respond to previous chemotherapy for advanced disease, cetuximab significantly improves overall survival (OS) and PFS compared to best supportive care alone [4]. More recently, it has been demonstrated that efficacy of cetuximab is significantly associated with a wild-type KRAS status [5,6]. Cetuximab is approved by the European Medicines Agency (EMEA) for the treatment of patients with EGFR expressing, KRAS wild-type metastatic colorectal cancer (in combination with chemotherapy as well as single-agent-therapy in patients who have failed oxaliplatin- and irinotecan-based therapy and who are intolerant to irinotecan). Nevertheless, there is still a group of patients with wild-type KRAS status that does not benefit from treatment with cetuximab, and additional mechanisms of resistance are assumed. Despite all advances, it is yet not possible to identify patients who will respond to cetuximab treatment upfront. Given the substantial therapy costs and the considerable rate of side effects (especially skin toxicity), improved strategies for identifying responders are needed. Patients who are responsive to cetuximab treatment may gain a tremendous benefit if combinations of chemotherapy and cetuximab are given in the first-line situation, because a switch from primarily palliative chemotherapeutic treatment to a curative surgical approach („conversion therapy") seems to be more prevalent in patients who are responsive to induction treatment [7].

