### Statistical considerations

#### Study hypothesis

The main hypothesis to be tested in the primary analysis is whether or not the relative change

(ΔSUV = 100⋅(SUV_Baseline_-SUV_d14_)/SUV_Baseline_) in the SUV from baseline to day 14 has any predictive relevance for early clinical response determined at day 56. This hypothesis is tested by comparing the groups of early clinical responders and nonresponders with respect to the quantitative variable ΔSUV using a Wilcoxon rank sum test (2-sided test, α = 5%)

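### The rule that keeps cetuximab-caused skin toxicity up to grade 3 out of AE reporting makes the planned AE frequency undercount a toxicity the article itself singles out

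*Protocol article*

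**What the plan says.** Three places in the protocol article bear on this point.

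- **Safety aspects and adverse events (AEs).** After predicting that "there are only few AEs to be expected", the section sets the exemption: "Skin toxicity ≤ grade 3 caused by cetuximab will not be reported as an AE". The next sentence says that "all AEs that occur after the patient has signed the informed consent document will be documented". The one after it reads: "All patients who have AEs, whether considered associated with the use of the trial medication or not, are monitored to determine the outcome". Neither of the last two mentions skin toxicity or refers back to the exemption.
- **Statistical analysis.** "The assessment of safety will be based mainly on the frequency of adverse events", together with laboratory values that leave pre-set ranges or worsen markedly from baseline.
- **Background.** Among the reasons for wanting better ways to identify responders, the article lists therapy costs and "the considerable rate of side effects (especially skin toxicity" in particular. It gives no percentage.

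**The concern.** A frequency of AEs can count only what is recorded as an AE. The exemption removes a whole class of drug-attributed event before the count is made. It is not confined to mild events, since its limit includes grade 3.

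Two things are at stake. First, the safety summary would show fewer events than occurred, in a class that the article itself picks out. Second, the exemption applies only to events judged to be caused by cetuximab, whereas the follow-up sentence disregards attribution. Whether a given skin event is counted therefore depends on a causality judgement made before it is recorded. After day 14 cetuximab is given together with Folfiri, so more than one drug is a candidate cause. Different assessors could record the same event differently.

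**Working it through.** The plan has no figure on this point to reproduce, so the check is mainly a reading of the text.

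**Step 1: which skin events reach the AE count under the literal rule?**

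| Event | Counted as an AE? |
|---|---|
| Skin toxicity, grade 1 to 3, attributed to cetuximab | No (exempted) |
| Skin toxicity above grade 3, attributed to cetuximab | Yes |
| Skin event of any grade, not attributed to cetuximab | Yes |

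So counted skin events = all skin events − those of grade 1 to 3 attributed to cetuximab. The subtracted term cannot be negative, so any error is an undercount.

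**Step 2: does another stated source recover them?** The Statistical analysis section names one other source, laboratory values, and these do not record skin reactions. The article describes no separate skin record or table. The word for mainly in that section leaves room for something else, but nothing else is named.

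**Step 3: do the neighbouring sentences restore them?** That depends on the reading.

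- If the exemption means that these events are not AEs, they fall outside the sentence on documenting all AEs, and the undercount in Step 1 follows.
- If reporting means only onward notification, and documenting means entry in the case report form, the events are recorded and can be counted. The text does not draw that distinction. It says the events are not reported *as an AE*.

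**Step 4: how large could the undercount be?** The documents give no rate, so this is illustration only.

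- Denominator: 35 evaluable patients with about 10% not evaluable (Sample size calculation) gives 35 / (1 − 0.10) = 38.9, that is 39, which matches the article.
- Patients with at least one exempted event = assumed rate × 39:
  - 30%: 0.30 × 39 = 11.7, about 12
  - 50%: 0.50 × 39 = 19.5, about 20
  - 70%: 0.70 × 39 = 27.3, about 27
  - 90%: 0.90 × 39 = 35.1, about 35

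The rates are assumptions and pool grades 1 to 3, so they do not size the loss of grade 3 events. It is the skin events that would be missing from the table; the patients may still appear there with other AEs.

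**Step 5: does the primary analysis change?** No. It compares ΔSUV between responders and nonresponders with a "Wilcoxon rank sum test (2-sided test, α = 5"%, and uses no AE data.

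**The case against.** The strongest reply is that there is no contradiction. A specific exclusion comes first and a general rule follows, so what has been taken out of AE status is not among all AEs. The verbs also differ, one sentence speaking of reporting and the other of documenting. This stands as far as it goes: a reader might infer that the two sentences flatly conflict, and the text does not establish that. It does not remove the point, because the first of these readings is the one that produces the undercount, and the second needs a distinction that the article does not state.

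The sponsor could also say that safety is not among the listed objectives, that no test or decision depends on AE frequency, and that the regimen is well known. All of this is fair and limits the severity. Familiarity may justify lighter notification, but it does not make a frequency table complete.

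Three further inferences are tempting and are not supported:

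- **Serious grade 3 skin events go unhandled.** The article has no section on serious events, but a condensed article commonly leaves that to the full protocol, which is not shown. Its silence proves nothing.
- **The undercount strikes what is new in the trial.** The Discussion claims novelty for metabolism and vascularization under single-agent cetuximab, not for safety. The exemption also applies throughout treatment, not only in the run-in.
- **The trial's benefit argument can no longer be assessed.** This single-arm study sets out no benefit–toxicity comparison, and the Discussion leaves the avoidance of unnecessary toxic treatment to further studies.

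**Conclusion.** The point holds, at moderate severity. Under the literal rule, the AE frequency on which safety mainly rests leaves out cetuximab-attributed skin toxicity of grades 1 to 3, severe grade 3 events included. The article states this rule outright, so the point does not rest on detail omitted from a condensed text.

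The conclusion assumes that the exemption governs what is counted and that no other record feeds the safety summary; the article names none. If the full protocol limits the exemption to onward notification, the undercount disappears and only the wording needs correction.

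The direction is certain under the literal reading, but the size is not known. The range in the working only shows how strongly the count depends on a rate that the article does not give. The sample size and the ΔSUV analysis are not touched.

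**What to change.** Reconcile the exemption with the sentence that follows it. The revised text should say that all skin toxicity, whatever its attributed cause, is recorded by grade and included in the safety tabulation. If lighter handling of expected skin reactions is wanted, limit it to onward reporting and say so. Recording should not depend on a prior causality judgement; attribution can be a separate field.

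Separate tables for the run-in and the combination phase are optional and not needed to correct the error.

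The cost is small but not nil: a graded skin item with a little extra data entry, a minor amendment to an already approved protocol, and retrospective capture for the 7 patients included at the time of writing. The remaining 39 − 7 = 32 planned patients would be recorded prospectively if the change were made at that point. It concerns recording and tabulation only and alters no treatment rule.
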